#### **What are your outcome measures?**

**Outcome measures:** All scales to measure outcomes are validated and were tested in the pilot study.

#### **Primary measures:**

- (1) Carers: SF-12 (Ware, Kosinski, & Keller, 1996): The SF-12 includes 12 items measuring two domains: mental health-related QoL and physical health-related QoL. Construct validity is 0.92 for the mental component and 0.91 for the physical component. The test-retest reliability for the mental component is 0.76 and for the physical component is 0.89. Higher scores indicate better QoL.
- (2) Care recipients' Quality of Life in Alzheimer's Disease (QOL-AD)-Proxy (Logsdon, Gibbons, McCurry, & Teri, 2002): This scale has 13 items. It has an internal consistency of 0.84-0.86 and test-retest reliability of 0.76-0.92. Higher scores indicate better QoL.

#### **Secondary measures:**

- (1) Caregiving Self-Efficacy Scale (Steffen, McKibbin, Zeiss, Gallagher-Thompson, & Bandura, 2002): This scale includes 3 subscales with 15 items: self-efficacy for obtaining respite, responding to atypical patient behaviours and controlling upsetting thoughts about caregiving. It shows internal consistency of 0.8 and test-retest reliability of 0.70. Higher scores indicate better self-efficacy.
- (2) Quality of support (Moholt, Friborg, Skaalvik, & Henriksen, 2018): It includes 5 items and shows an internal consistency of 0.76 and test-retest reliability of 0.80. Higher scores indicate better social support.
- (3) The Revised Memory and Behaviour Problem Checklist (Teri et al., 1992): It includes 24 items measuring the frequency of memory and behaviour problems of PLWD and carers' reaction to those problems in three subscales: depression, disruption and memory-related problems. It has an internal consistency of 0.84 for frequency of behaviour and 0.90 for reaction to the behaviour and construct validity. Lower scores indicate less frequency of memory and behaviour problems and carers feeling less upset.

#### **Measures for cost-effectiveness:**

- (1) The primary measure of cost-effectiveness will be the incremental gains in QALYs from the perspective of carers and people with dementia compared to usual care.

Resources associated with the development and implementation of the intervention will be documented and costed according to established best practice guidelines (Drummond et al., 2015). SF-12 responses between baseline and 12 months will be converted into health state utilities for the calculation of QALYs for carers using the SF-6D preference-based scoring algorithm developed by Brazier et al. (Brazier, [name], Salomon J, & Tsuchiya, 2017). QOL-AD-Proxy responses will be similarly converted using the preference-based scoring algorithm developed by Comans et al. (Comans et al., 2020).

- (2) Linked administrative health data from Data Linkage Services, including Pharmaceutical Benefits Scheme (PBS) and Medicare Benefits Schedule (MBS) utilisation, and hospital and emergency department uses, will be used to capture health service use for PLWD and their carers for 12 months prior and 12 months post recruitment with permission of the carers and their care recipients (when appropriate). Pre-baseline resource use data will provide additional baseline variables to control for potential confounding. The difference between pre- and post-baseline use of health services will be used to measure changes in PLWD's levels of utilisation and cost of health services in both study arms.
- (3) Data on health and social care visits outside those provided by MBS will be collected from participants using the resource utilisation in dementia (RUD) questionnaire (Wimo, Wetterholm, Mastey, & Winblad, 1998).
- (4) Unit costs will be derived from hospital finance departments and Australian Refined Diagnosis Related Groups cost weights. Cost of nursing home care will be calculated using basic daily and accommodation fees apportioned according to length of stay.

**Carers' experiences in the iSupport for Dementia program:**

Carers' experiences in intervention program will be explored by analysing audio-recorded monthly Zoom video meetings with the program facilitators and their peers in the intervention group. The messages (text messages via mobile, email and WhatsApp, request for support) and time spent by facilitator to provide the support will be documented and analysed. Facilitators will document their assessment of carers' needs, actions to meet carers' needs and outcomes in a structured facilitator portfolio (see attachment: Facilitator portfolio) and submit to the project team as part of data for analysing carers' experience in the trial. Facilitators will use code for study site and pseudonyms for carers in the portfolios to maintain confidentiality of information for carers. A descriptive qualitative study design using thematic analysis will be applied

to achieve this study objective. Findings will be reported as themes that represent carers' learning experiences.

**Project duration:**

The intervention will last 12 months. To include time for participants recruitment, we anticipate this study will last 18-24 months.

**Participant selection and activities**

Explain how participants will be recruited or how their data will be selected (e.g. for a registry).

Describe sources and methods that will be employed in the identification and recruitment/selection of potential participants (e.g., clinics, referring doctors, adverts, and time periods) or of historical data (e.g. medical records, databases).

You should make a distinction between how you will recruit/select control participants compared to other groups if performing a comparative intervention.

**How many participants will be selected for the study?**

Based on sample size calculation, 184 carers in total. We plan to recruit 46 carers (23 in each arm) in each of the 4 study sites.

**How are they identified as possible participants?**

**SALHN and Canberra Health Services:**

Based on inclusion and exclusion criteria, carer participants will be identified by clinicians from various care settings, for example in the memory and geriatric clinics, aged care and dementia care wards, ambulatory geriatric services and falls clinic. We will also publish recruitment flyer on social media to recruit participants via these recruitment sites.

**Bolton Clarke Victoria and Resthaven SA:**

Staff in community aged care settings will identify potential participants by checking the database of their clients.

**Community**

1) Contact the local council to distribute recruitment flyers to their support/activity groups (i.e., but not limited to Mitcham council, Onkaparinga council); 2) Put up flyers on social media (i.e., Facebook and Twitter); 3) Put up flyers on the notice board in the community (i.e., library and supermarket notice board); 4) Distribute flyers to local church group; 5) Distribute flyers to super GP clinic; 6) Contact Canberra Health Services' collaborative organisations and community organisations in Canberra and surrounding regions (i.e., but not limited to Dementia Australia, CarersACT, Health

Care Consumers Association, ACT Disability Aged and Carer Advocacy Service (ADACAS), and Multicultural Association of Canberra) to disseminate study details (e.g., via newsletters, posters, presentations). 7) Disseminate study details to care settings outside of Canberra Health Services in Canberra and surrounding regions (e.g., private geriatric clinics in Canberra)

Pre-screen for eligibility – waiver of consent

The recruitment method must be compliant with the Health Care Act 2008. If you need to access a patient's medical records to pre-screen for eligible participants, and you do not have prior patient consent to do so or are not part of the patient's clinical care team, you will need to apply for an exemption under 93(3)(f).

Are you requesting a waiver of consent to pre-screen?

☐ No

☒ Yes

Under s93(3),(f) of the Health Care Act 2008, we wish to apply for an exemption of patient consent to access their personal information for research purposes.

**How will participants be recruited into the study?** Please provide a detailed step by step description of the recruitment methods i.e. flyers, adverts, direct approach, invitation letter etc.

**How will they be approached?** Which staff / research team members are approaching the participants? When is this occurring? I.e. clinic, inpatient.

### **SALHN and Canberra Health Services:**

#### **(1) Participant identification:**

- a. A recruitment flyer (Appendix A) will be put on various care settings described above where clinicians will help the researchers identify potential participants. Clinicians (or a site-specific researcher at Canberra Health Services) will identify potential participants based on the inclusion and exclusion criteria, distribute the flyer to them and ask if potential carer participants would like to be contacted by a site-specific researcher. After they have gained carers' permission, researcher, [name], (or a site-specific researcher at Canberra Health Services) will talk to potential carer about the study and undertake eligibility check.
- b. We will also publish recruitment flyer on social media such as Facebook and newsletters via the recruitment sites.
- c. Database will be screened by clinicians (or a site-specific researcher at Canberra Health Services) to identify potential participants in various care settings, for

example the memory and geriatric clinics, aged care and dementia care wards, ambulatory geriatric services and falls clinic. Due to the covid restriction, potential participants may not be able to come to clinics for face-to-face follow-up.

Therefore, we will use various methods (i.e., posting or emailing the Flyer or talk to them by phone) to gain their expression of interest in the study. They decide whether they would like to participate in the study.

- (2) **Eligibility check:** The researcher will check with carer if their care recipient would be interested and available to be assessed. If not, the researcher will undertake cognitive assessment for the care recipients based on carers observation using Global Deterioration Stage between normal ageing and Alzheimer's disease
- (3) **Capacity to Consent:** The researcher will check with carer if their care recipient would be interested in and available to be assessed. If yes, the researcher will also use the 'Evaluation to Sign Consent' (Appendix B) (Resnick et al., 2007) to assess the capacity of the care recipients to provide consent for MBS and PBS data used in the study. It will take only 5 minutes for the researcher to complete the assessment. If answer is no, there is no need to do this assessment.
- (4) **Explanation:** For potential carer participants who have met the inclusion criteria, the researcher [name] (or a site-specific researcher at Canberra Health Services) will provide them with Information Pack including Participant Information Sheet and Consent Form (PICF) (Appendix C). The researcher will also provide the care recipients with simplified PICF (Appendix D). The researcher will explain details of the research project (including their rights to withdraw) and answer questions.
- (5) **Informed consent:** The researcher will contact potential carer participants and their care recipients (only if they want to be involved) at least 24 hours (a maximum of 3 days) to confirm their participation and will meet them face-to-face or online to sign a written consent including the consent for MBS and PBS data used in the study. For the care recipients, a verbal consent will be recorded using voice recorder with their informal carer presents. This is to ensure the conversation can be replayed to the care recipients if cognitive condition declines at the later dates.
- (6) **Third-party consent:** If the care recipients have no capacity to make decision to sign consent as indicated by the assessment using the 'Evaluation to Sign Consent', the carers will be requested to be the third-party to sign the consent form (See Appendix D) for sharing information about the care recipients' health resources use using 'The resource utilization for dementia care (RUD) questionnaire' (see Appendix G). In addition, the researcher will also request the carers (or other persons when appropriate), who have a written enduring power of

attorney or legal guardianship documents, to be the third-party to sign the consent form for the person with dementia to allow Services Australia to release MBS/PBS information used in the study (See Appendix E). If the care recipient is not interested in the study, we will not collect information related to the care recipient's 'The resource utilization for dementia care (RUD) questionnaire' (see Appendix G) and MBS/PBS.

**Bolton Clarke Victoria and Resthaven SA:**

- (1) **Participant identification:** In community aged care managed by Bolton Clarke Victoria and Resthaven SA, staff will identify potential participants by checking the database of clients, distribute a recruitment flyer to potential carer participants and ask if they would like to be contacted by a site-specific researcher. After they have gained carers' permission, researcher, [name], (or a site-specific researcher at Bolton Clarke) will talk to potential carer about the study and undertake eligibility check.
- (2) **Eligibility check:** same as described above.
- (3) **Capacity to Consent:** same as described above.
- (4) **Explanation:** same as described above.
- (5) **Informed consent:** same as described above.
- (6) **Third-party consent:** same as described above.

**Community**

- (1) Participant identification: Participant will contact researcher (contacts will be provided via flyer) to gain further information. Researcher, [name], (or a site-specific researcher at Canberra Health service or Bolton Clarke) will talk to potential participants about the study and undertake eligibility check.
- (2) Eligibility check: same as described above.
- (3) Capacity to Consent: same as described above.
- (4) Explanation: same as described above.
- (5) Informed consent: same as described above.
- (6) Third-party consent: same as described above.

**What are the inclusion and exclusion criteria?** - Detail the characteristics that clearly describe the study population that are required to be either included or excluded in the research.

The study population is informal carers of community-dwelling people living with dementia (PLWD).

**Inclusion criteria**

The carer need to meet these conditions: (1) The carer is aged 18 years or over; (2) The carer provides care support for an adult person at home living with dementia at least twice a week; (3) if a care recipient has no formal dementia diagnosis but meets the following three criteria: a) cognitive impairment using valid tools such as MMSE to measure (scored <24) or other validated tools Global Deterioration Stage between normal ageing and Alzheimer's disease (GDS), or RUDAS) to measure (Independent Hospital Pricing Authority, 2014; Reisberg, Ferris, de Leon, & Crook, 1982; Storey, Rowland, Conforti, & Dickson, 2004); b) self-care decline and c) changed behaviours using the valid 'Blessed Dementia Dependence Score' (Blessed, Tomlinson, & Roth, 1968).

**Exclusion criteria**

Carers will be excluded if they (1) have health conditions that may significantly impact their ability to participate in the study; (2) involve in other studies, and (3) cannot read English without additional assistance.

**Participant commitment** -What will their participation involve? I.e. study visits, procedures, tests, tissue samples, questionnaires, wearing of any devices.

**Arm 1–Usual care group:** Carers will receive the usual carer support provided by Dementia Australia or other publicly funded carer support. They will receive a monthly reminder email that directs them to the Dementia Australia website where they can seek support if they so wish. Carers will undertake an online survey (Appendix F) at three time points: baseline, 6 months and 12 months. They will be notified about each survey by email and an SMS message. Carer can reply 'stop' to indicate the termination of the reminder and withdrawing from the study. Each survey will take about 30 minutes. Carers will also undertake a monthly 10-minute survey to document the previous month health care services utilisation (Appendix G). Therefore, the time commitment for this group of carers would be no more than 9 hours.

**Arm 2–Intervention group:** Carers will engage in these activities:

- (1) Managing transitions: In each study site, carers will be assigned to an iSupport program facilitator and encouraged to request individualised support from the facilitator during transition between care settings (i.e. from hospital to home transitional care) and care types (i.e. receiving ambulatory geriatric services, or rehabilitation or palliative care at home in addition to usual home care package).
- (2) Managing dementia progression: Carers are also encouraged to contact the facilitator to discuss changes in PLWD (i.e. signs of deterioration, changed

behaviours and complications) and gain advice to access relevant multidisciplinary care services for timely treatment and care. The facilitator will follow the carers until their needs for support have been met.

- (3) Psychoeducation: Carers will select at least 20 out of 30 learning units from the that are relevant to them from the online iSupport program or a hardcopy of iSupport handbook to learn over the first 6 months of the trial and revisit or learn new units when they feel it is needed in the second 6 months. The expected time spent on their engagement with the online iSupport learning units will be no more than 12 hours in total. The completion of each unit will be measured through the program design and will be recorded as data for compliance with the intervention. Carers will receive a certificate for each unit they complete, a strategy to motivate them in the program.
- (4) Carer support group: In each study site, the facilitator will assign the 23 carers into one of two support groups. The facilitator will conduct a monthly online carer support group meeting lasting no more than 30 minutes. Managing transitions between care settings and types and managing disease progression will be standard meeting agenda so that carers can share their experiences and support each other in these dementia caregiving areas. The meetings will be recorded for carers in the same group to access. The facilitator will also create carer support groups in WhatsApp to encourage carers to talk or send text messages to their peers in the same group to strengthen social support. Facilitator will communicate with participants via phone calls if they have no access to zoom or WhatsApp. The facilitator will analyse group interactions, investigate carers' needs for support and provide feedback to them.
- (5) Feedback on services: The facilitators will collect carers' feedback via regular carer support group meetings, and discuss the feedback in their organisation's quality improvement meetings.
- (6) Confidentiality: Carers will follow an agreed protocol to maintain confidentiality and privacy in group activities.
- (7) Carers will undertake an online survey at three time points: baseline, 6 months, and 12 months. Each survey will take about 30 minutes. Carers will also undertake a monthly 10-minute survey (online or hardcopy) to document the previous month health care services utilisation. They will be notified about each survey by email and an SMS message sent by the researcher. Carer can reply 'stop' to indicate the termination of the reminder and withdrawing from the study. Therefore, the time commitment for this group of carers would be no more than 27 hours.

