***Randomisation and interventions***

After baseline data collection, carers will be randomly assigned to receive either the iSupport program or the usual care. To ensure the two groups are of equivalent size and conditions, a block randomisation will be used to allocate carers to one of the two treatment groups for each recruitment site. Stratification will also be used in the block randomisation to ensure equivalent distribution of spouse carers versus non-spouse carers and care recipients with mild versus moderate dementia in each treatment group.

**Arm 1–Usual care group:** Carers will receive the usual carer support provided by Dementia Australia or other publicly funded carer support. They will receive a monthly reminder email that directs them to the Dementia Australia website where they can seek support if they wish.

**Arm 2–Intervention group:** The planned interventions are described in the following.

- (1) Managing transitions: In each study site, carers will be assigned to an iSupport program facilitator and encouraged to request individualised support from the facilitator during transition between care settings (i.e. from hospital to home transitional care) and types (i.e. receiving ambulatory geriatric services, or rehabilitation or palliative care at home in addition to usual home care package) of the PLWD.
- (2) Managing dementia progression: Carers are also encouraged to contact the facilitator to discuss changes in PLWD (i.e., signs of deterioration, changed behaviours and complications) and gain advice to access relevant multidisciplinary care services for timely treatment and care. The facilitator will follow the carers until their needs for support have been met.
- (3) Psychoeducation: Carers will select at least 20 out of 30 learning units that are relevant to them from the online iSupport program to learn over the first 6 months of the trial and revisit or learn new units when they feel it is needed in the second 6 months. The expected time spent on learning the online iSupport learning modules

is no more than 12 hours in total. The completion of each unit will be measured through the program design and will be recorded as data for compliance with the intervention. Carers will receive a certificate for each unit they complete, a strategy to motivate them in the program.

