In addition, the 'Partnership in iSupport program' is an innovative patient-centred care model that targets the organisation's structures, resources and processes to improve care services. The program will be implemented by four industry partners in the project. Findings will provide evidence on the efficacy of an online education program in dementia care and in virtual social support that meet carers' needs. This program is designed to help carers seek practical solutions to their individual issues from the service provider and peers in a timely manner to prevent care crises that may trigger hospital admission, emergency department use and premature admission to residential aged care homes. The program is also designed to improve reach to carers in rural and remote areas and to carers of working age. The COVID-19 pandemic has highlighted the urgent need to have programs such as iSupport which are not impacted by lockdowns.

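### A hardcopy handbook is allowed in one description of the intervention and not in the other, and no way of recording units read on paper is given, so compliance data for handbook users would be under-recorded or missing

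*Protocol*

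**What the plan says.** The psychoeducation component of the intervention arm is described twice in the protocol.

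- **Randomisation and interventions, Arm 2, item 3:** "Carers will select at least 20 out of 30 learning units that are relevant to them from the online iSupport program". The online program is the only source of units named.
- **Participant commitment, Arm 2, item 3:** the 20-of-30 target is repeated, but the source is now the "online iSupport program or a hardcopy of iSupport handbook to learn over the first 6 months of the trial".

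Both items then say: "The completion of each unit will be measured through the program design and will be recorded as data for compliance with the intervention". Neither defines the program design or says how it would register a unit studied on paper.

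Two neighbouring sentences under Participant commitment also bear on the point. The time estimate is tied to the online units: "The expected time spent on their engagement with the online iSupport learning units will be no more than 12 hours in total". The certificate is promised without regard to format: "Carers will receive a certificate for each unit they complete, a strategy to motivate them in the program".

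**The concern.** The protocol commits to recording unit completion as compliance data and sets a numerical target for it. The method named for recording completion fits the online program. One of the two descriptions adds a paper route and leaves the method unchanged. If paper readers are not captured, the compliance figure for the arm is wrong in a way that depends on who chose paper, and those are likely to be the carers least able to use the platform.

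What is at stake is the description of uptake. In a self-paced program, a reader of a null result will want to know how far carers engaged with the material, and unit completion is one of the records that would help answer that. A unit read on paper and not noted during the trial cannot be recovered later by an analysis plan.

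**Working it through.** The protocol states no figure here to reproduce. The check is mainly a comparison of text, followed by an illustration of size.

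**Step 1: format.** Randomisation and interventions offers units "from the online iSupport program to learn over the first 6 months of the trial". Participant commitment offers the online program or the handbook, for the same arm, component and period. The two items differ on what may be used.

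**Step 2: meaning of the recording sentence.** The wording is identical in both items. In the first, only an online program exists for it to refer to. The natural reading is tracking by that program, and the second item carries the sentence over unchanged.

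**Step 3: any other record of units.** The sections that might hold one were read in turn.

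| Protocol section | What is recorded | Unit completion? |
|---|---|---|
| Carers' experiences in the iSupport for Dementia program | Meetings, messages, facilitator time; facilitator portfolio of needs, actions and outcomes | Not mentioned |
| Participant commitment and Participant follow up | Surveys at baseline, 6 and 12 months; monthly 10-minute survey of service use | Not mentioned |
| Data management (data-collection items) | Demographics, service use, outcome surveys, group meetings, messages, MBS/PBS data | Not mentioned |

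The survey forms and the facilitator portfolio are attachments that are not shown, so this step covers the protocol text only.

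**Step 4: size, as illustration only.** Inputs: 92 carers per group (Sample size section) and the target of 20 units. Assumptions, none of them in the protocol:

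- a hardcopy share h of 5% to 30%;
- every carer truly completes 20 units;
- handbook users never use the online program.

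If paper readers are coded zero:

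- carers affected = 92 × h
- recorded mean = 20 × (1 − h)
- share recorded as reaching 20 units = 1 − h

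| h | Carers affected | Recorded mean (true 20) | Recorded as reaching 20 (true 100%) |
|---|---|---|---|
| 5% | 4.6 | 19 | 95% |
| 10% | 9.2 | 18 | 90% |
| 20% | 18.4 | 16 | 80% |
| 30% | 27.6 | 14 | 70% |

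If paper readers are coded missing, the recorded mean is the online users' mean, m_online, while the true arm mean is (1 − h) × m_online + h × m_paper. The error is h × (m_online − m_paper). It is zero if the two groups complete equally and can go either way otherwise. In that case the figure describes 92 × (1 − h) carers and not the arm.

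**The case against.** The strongest reply has four parts.

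1. **The protocol does not say that completion is captured only by the platform, or that a handbook user scores zero.** This stands. A reader might infer that paper readers would be recorded as completing nothing, but the text does not fix the coding: zero, missing or some other report are all open. The certificate promised for every completed unit even presupposes some way of knowing that a unit was done. What remains is that no such way is described for paper, and neither zero nor missing gives a valid figure for the whole arm.

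2. **The unseen attachments might contain a unit log.** This is possible and cannot be excluded. But the protocol text names a method, and that method does not fit one of the formats it allows. This goes beyond detail left to the SAP, because it concerns what is collected during the trial.

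3. **The likely number of handbook users is not known.** This also stands. A reader might take the Sample size section's statement that more than 80% of carers use email with care staff to mean that up to 20% of participants are offline. That figure is given to support recruitment, describes carers at the partner organisations, and concerns emailing staff, not internet access. The outcome surveys are themselves described as online. The remark about carers without internet or a smartphone is a contingency for the support groups, not a forecast of learning format.

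4. **Nothing in the main results depends on the measure.** Correct. Outcomes are analysed by intention to treat, and no analysis by units completed is stated. The program also includes a link worker and support groups, for which messages and facilitator time are documented separately, so unit completion is not the only evidence on uptake.

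A reader might also set the handbook against the statement under Benefits that "Findings will provide evidence on the efficacy of an online education program in dementia care" and see a conflict over what the trial tests. That sentence is an expected benefit, not a hypothesis, and the Hypothesis section does not make online format the thing under test. It does not support a separate point.

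**Conclusion.** The point holds in a limited form. The two descriptions of psychoeducation differ on whether a handbook may be used. The only stated way of recording completion is written for the online program, and nothing in the protocol text records units read on paper. Compliance against the 20-of-30 target would therefore be biased downwards if handbook users are coded zero, or restricted to online users if they are coded missing.

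The size cannot be determined because the hardcopy share is not given. The range above (a recorded mean of 19 down to 14 units against a true 20) rests entirely on the assumed 5% to 30% share, equal completion of 20 units, no online use by handbook readers, and zero coding. The primary, secondary and cost-effectiveness comparisons are not affected. Severity is low; the change is a cheap improvement, best made before data are collected.

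**What to change.** - Reconcile item 3 of Arm 2 under Randomisation and interventions with item 3 under Participant commitment, so that both state the same format or formats.
- If hardcopy remains, record each intervention carer's format (online, handbook or both).
- Add a short self-reported unit checklist for handbook users to the monthly survey, which already exists online and on paper. Keep it as a separate page for those carers, so that the service-use questions stay the same in both arms.
- Define completion as units completed from either source, counting a unit once, and report compliance by format.

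The cost is a wording change and one brief checklist. The downside is that paper completion is self-reported and less objective than platform logs, so it should be flagged as such wherever compliance is reported.
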